#### Sample size calculation

The 2-year OS in each arm, based on the results of ORATOR, is estimated to be 94%. A 2-year OS of < 85% will be considered inadequate. In order to differentiate an OS of 94% vs. 84% using a 1-sided one-sample binomial test, with 80% power and alpha of 0.05, with 10% dropout, 70 patients are needed in each arm (140 total).

#### Analysis plan

Patients will be analyzed in the groups to which they are assigned (intention-to-treat). Comparisons of OS and PFS with historical controls will be evaluated using a one-sided binomial test. The 2-year PFS in this cohort is estimated to be approximately 85%, based on the results of CCTG HN6 [22]. If the 2-year PFS is < 75%, it will be considered unacceptable. Therefore, PFS in each arm will be compared against a benchmark PFS of 74%. A comparison of OS and PFS between the two treatment arms will also be conducted, using the stratified log-rank test (stratified by smoking pack-year history). With a sample size of 140 patients, we will have 80% power to detect a 10% superiority in OS in either arm (assuming baseline OS of 94% in whichever arm is superior), using a two-sided alpha of 0.05. A two-sample T-test will be used to compare QOL scores at 1-year (excluding PNQ). The percentage of patients in each arm who experience a clinically significant QOL decline (10 points) will also be reported. Pre-planned subgroup analysis will occur based on the stratification variable (smoking pack-year history). A Cox proportional hazards multivariable regression analysis will be used to determine baseline factors predictive of survival. QOL analysis for secondary endpoints will be performed in the same way as the ORATOR trial using linear mixed-effects models [24]. The original ORATOR trial will be used for additional historical controls [12]. A comparison will occur between HPV+ patients in ORATOR (who were treated with more aggressive approaches) and ORATOR2 to assess differences in QOL and time-to-event outcomes.

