### Primary endpoint

OS
◦ Defined as time from randomization to death from any cause

This study was originally launched with a primary endpoint of PFS. The results of the original ORATOR trial became available in February 2019. These suggested that OS would be a preferred endpoint for ORATOR2 as both arms in ORATOR showed excellent OS in p16+ cancers (both > 92% at 2 years). OS is preferred as the primary endpoint to evaluate de-escalation, since it was evident in ORATOR that progression events, whether local, regional, or distant, can often be salvaged for cure with surgery, radiation, or systemic therapy including immunotherapy. Therefore, in Feb 2019, without knowledge of outcomes data from ORATOR2, this trial was amended to promote OS from a secondary to primary endpoint, and demote PFS to a secondary endpoint.

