### Subject discontinuation / withdrawal

Subjects may voluntarily discontinue participation in the study at any time. If a subject is removed from the study, the clinical and laboratory evaluations that would have been performed at the end of the study should be obtained. If a subject is removed because of an adverse event, they should remain under medical observation as long as deemed appropriate by the treating physician.

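### Time-to-event OS with 10% expected dropout is tested by a binomial test that cannot use patients censored before 24 months; a Kaplan-Meier bound would serve better

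*Protocol article*

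**What the plan says.** All references are to the protocol article.

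- **Primary endpoint:** OS is "Defined as time from randomization to death from any cause", so it is a time-to-event variable.
- **Sample size calculation:** the expected rate, in per cent, is given as "The 2-year OS in each arm, based on the results of ORATOR, is estimated to be 94". The planned test sets this rate against 84% in a single-arm, one-sided binomial comparison. The targets and the resulting size read: "with 80% power and alpha of 0.05, with 10% dropout, 70 patients are needed in each arm (140 total".
- **Analysis plan:** on the analysis population, "Patients will be analyzed in the groups to which they are assigned (intention-to-treat". For the benchmark comparisons of both OS and PFS: "Comparisons of OS and PFS with historical controls will be evaluated using a one-sided binomial test". The log-rank test and Cox regression are named only for the between-arm comparison and for baseline factors.
- **Subject discontinuation / withdrawal:** "If a subject is removed from the study, the clinical and laboratory evaluations that would have been performed" at study end should be obtained. Vital status at 24 months is not mentioned.

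**The concern.** A binomial test takes one yes/no value per patient. A patient last seen alive at 14 months has no such value at 24 months and must be dropped or given a status. Each choice has a cost.

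- **Dropping the patient** discards 14 months of follow-up. It also tilts the count towards deaths: a patient who dies while under observation always counts, whereas a survivor can be lost afterwards and leave the denominator.
- **Counting the patient as alive** gives credit for survival that was not observed.

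With about 7 of 70 patients per arm allowed for as dropouts and at most 5 deaths permitted, the counting rule can change whether an arm passes. The protocol already uses censoring-aware methods between the arms. Its interim look at 2-year OS, once half the patients have 6 months of follow-up, also needs one. Only the benchmark tests, including the primary one, do without.

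**Working it through.** **Inputs.** From the Sample size calculation: p1 = 0.94, p0 = 0.84, one-sided alpha 0.05, power 80%, 10% dropout, 70 per arm. Assumed, because the article does not give them: exponential death and exponential loss, independent of each other, with 10% lost by 24 months.

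**Step 1. Reproduce the stated size.** Let D be the deaths among n evaluable patients. An arm passes if D ≤ d, with d the largest value for which P(D ≤ d | n, 0.16) ≤ 0.05. Power is P(D ≤ d | n, 0.06).

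| n evaluable | d | type I error | power |
|---|---|---|---|
| 62 | 4 | 0.022 | 68.5% |
| 63 | 5 | 0.049 | 82.4% |
| 64 | 5 | 0.044 | 81.5% |
| 65 | 5 | 0.040 | 80.6% |
| 66 | 5 | 0.036 | 79.6% |
| 68 | 5 | 0.029 | 77.7% |
| 70 | 5 | 0.024 | 75.7% |

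The smallest n that meets both targets is 63, and 63 / (1 − 0.10) = 70. The stated figure is reproduced.

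Two things follow. The design treats lost patients as not evaluable. And the pass mark stays at 5 deaths from 63 to 70 evaluable, so power falls as follow-up improves. That fall is due to discreteness, not to censoring.

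**Step 2. Effect of the counting rule.** I simulated 70 patients per arm (40,000 arms) with the assumed loss and null 84%.

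| Handling of patients lost before 24 months | power, truth 94% | mean estimate, truth 94% | type I error, truth 84% |
|---|---|---|---|
| Excluded, binomial | 73.9% | 93.7% | 2.7% |
| Counted alive, binomial | 79.4% | 94.3% | 3.5% |
| Censored, Kaplan-Meier with log-log bound | 79.1% | 94.0% | 3.4% |

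Separate runs under the same assumptions gave 73-74% for exclusion, 78-79% for Kaplan-Meier, and a Kaplan-Meier type I error of up to 3.7%. Exclusion and counted-alive gave different verdicts in about 5-6% of arms at 94%; in every such arm of my run, counting as alive passed and exclusion failed.

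The loss model matters. Suppose status is missing for a random 10% whether or not the patient has died. Exclusion then averages 76.6% power. Counting as alive lowers the apparent death rate under the null to 0.16 × 0.90 = 0.144, and P(D ≤ 5 | 70, 0.144) = 0.051. At 15% loss the type I error is 0.073.

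**Step 3. The alternative.** S = ∏(1 − d_i/n_i) over death times up to 24 months. Greenwood sum V = Σ d_i / [n_i(n_i − d_i)]. Standard error on the log-log scale: se = √V / |log S|. Lower bound: S^exp(1.645 × se). The arm passes if the bound exceeds 0.84.

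With no loss, this rule gave 75.9% power and 2.3% type I error in simulation, against 75.7% and 2.4% for the exact test at 70. Nothing is given up when follow-up is complete. The scale matters: an untransformed bound had a type I error of 7.6% at 10% loss and 10.8% with no loss.

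**The case against.** A binomial test of a 2-year rate is a recognised single-arm phase II design, and the article names the same test for sample size and analysis. Ten per cent is a planning allowance. Visits every 3 months to 2 years, with follow-up to 5 years, may leave fewer than 7 patients per arm with unknown status. The bias from exclusion is about 0.3 points and conservative. The intention-to-treat sentence concerns the group in which a patient is analysed and does not by itself fix the denominator. How unknown status is counted may stand in a full protocol or SAP not shown here. All of this stands, and it limits the point to a better choice of method.

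Three stronger readings are tempting, and the document does not support them.

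- **That the stated 80% power is not delivered.** The 10% is already in the 70, and the planned 63 evaluable patients give 82.4%. The 75.7-79.6% at 66-70 evaluable comes from discreteness; at 70 nobody is censored.
- **That success becomes nearly impossible.** Power of about 3% arises only if every lost patient is counted as dead. The article proposes no such rule, and inflating 63 to 70 points to exclusion.
- **That Kaplan-Meier restores the power.** At about 78-79% it does not reach 80% either.

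What the objection does not remove is that the article does fix a test, and that this test cannot use censored follow-up on a time-to-event endpoint for which losses are expected.

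**Conclusion.** The point holds as a mismatch between endpoint and test, for OS and in the same way for PFS. Under an assumed random 10% loss, exclusion costs about 5 points of power against the Kaplan-Meier rule (73-74% against 78-79%) and lowers the estimate by 0.3-0.4 points. The choice between excluding and counting alive changes the verdict in roughly one simulated arm in twenty. With less loss these effects shrink.

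The sample size is correctly derived for its stated inputs. Its power is better described as roughly 75-80%, since 80% is met only at 63-65 evaluable within the planned range.

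All OS figures use the 84% benchmark of the calculation. The article also says "A 2-year OS of < 85% will be considered inadequate"; which of the two values is tested is a separate matter. The simulated figures rest on exponential times and non-informative loss.

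**What to change.** 1. **Primary analysis.** Estimate 24-month OS by Kaplan-Meier from all randomised patients in each arm, and declare success if the one-sided 95% log-log lower bound exceeds the benchmark. Name the log-log scale. State a rule for an arm without deaths, where the bound is undefined; with complete follow-up at 94% this has probability 0.94^70 = 1.3%, and an exact binomial bound would serve.
2. **PFS.** Use the same method against its 74% benchmark.
3. **Sensitivity analysis.** Keep the one-sided binomial test, and state how patients without 24-month status are counted.
4. **Withdrawal section.** Obtain 24-month vital status from records for patients who stop visits, unless consent for this is withdrawn.
5. **Power statement.** Describe power as roughly 75-80%, depending on the number evaluable.

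The cost is wording and record checks, with no extra patients. The downsides are modest: the bound is asymptotic (simulated type I error stays below 5%), it still assumes non-informative censoring, which is why item 4 matters, and it does not by itself bring power to 80%.

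### The 80% power claimed for the between-arm overall survival comparison is wrong at 2 years: 70 patients per arm give about 45-50%

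*Protocol article*

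**What the plan says.** The Analysis plan section of the protocol article has the two arms compared on OS and progression-free survival by a log-rank test stratified by smoking history. It then states the power for OS: "With a sample size of 140 patients, we will have 80% power to detect a 10% superiority in OS in either arm". The better arm is taken to have 94% OS, and the test is two-sided at the 0.05 level. The alternative is therefore 94% vs 84%.

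That sentence names no time point, but two other sections do. Sample size calculation gives 94% as the expected 2-year OS in each arm. Secondary endpoints lists the OS comparison between Arm 1 and Arm 2 as a 2-year comparison.

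The 140 patients were not derived for this comparison. Sample size calculation derives 70 per arm, allowing 10% dropout, for a test of each arm against a fixed benchmark at 80% power and alpha 0.05: "In order to differentiate an OS of 94% vs. 84% using a 1-sided one-sample binomial test".

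**The concern.** The between-arm claim has the same two rates, the same patients and the same 80% as the one-sample calculation, yet it describes a harder problem. A one-sample test compares one estimated proportion with a fixed number. A two-sample test carries sampling error from both arms, and here it is also two-sided rather than one-sided. The same sample size cannot give the same power for both. Carry-over from the one-sample calculation is a plausible explanation, but the document does not say where the figure came from.

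Comparing survival between the two approaches is a stated goal of the trial, and its results are meant to inform phase III designs. Beside an 80% power claim, a non-significant OS result invites the reading that a 10-point deficit has been reasonably excluded. At the true power it would not have been.

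**Working it through.** **Inputs from the protocol.** OS of 94% in the better arm, a difference of 10 points, two-sided alpha 0.05 and the log-rank test (Analysis plan); 2 years as the time point (Sample size calculation, Secondary endpoints); 70 per arm and 10% dropout, so 70 × 0.9 = 63 evaluable per arm (Sample size calculation). Exponential survival is assumed wherever a hazard is needed.

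**1. The one-sample figure reproduces.** With 63 evaluable patients in one arm and success declared at 58 or more alive, the exact one-sided alpha at 84% is 0.049 and the power at 94% is 82.4%. The primary calculation stands.

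**2. Two proportions at 2 years, 70 per arm.** The pooled rate is (0.94 + 0.84)/2 = 0.89.
- Null SE = √(2 × 0.89 × 0.11 / 70) = 0.0529
- Alternative SE = √((0.94 × 0.06 + 0.84 × 0.16) / 70) = 0.0522
- Power = Φ[(0.10 − 1.96 × 0.0529) / 0.0522] = Φ(−0.07) = 47.2%

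With 63 per arm the same formula gives 43.3%.

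**3. Log-rank at 2 years.**
- Hazard ratio = ln(0.84)/ln(0.94) = 2.82 (0.355 the other way round)
- Expected deaths by 24 months = 70 × (0.06 + 0.16) = 15.4
- Schoenfeld power = Φ[½ × √15.4 × ln 2.82 − 1.96] = Φ(0.07) = 52.9%
- Freedman power = Φ[√15.4 × (2.82 − 1)/(2.82 + 1) − 1.96] = Φ(−0.09) = 46.4%

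**4. Other methods.** Two-sided 0.05, 2 years; the log-rank simulation is unstratified, 6,000 runs.

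| Method | 70 per arm | 63 per arm |
|---|---|---|
| Pooled z | 47.2% | 43.3% |
| Unpooled z | 48.2% | 44.3% |
| Arcsine | 49.2% | 45.3% |
| Chi-square, exact power | 48.3% | 44.2% |
| Fisher | 38.0% | 32.9% |
| Log-rank, Freedman | 46.4% | 42.6% |
| Log-rank, Schoenfeld | 52.9% | 48.7% |
| Log-rank, simulated | 47.8% | 44.6% |

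A one-sided 0.05 test does not recover the claim: 59-65% at 70 per arm. Nor does reading the 10% as relative (94% vs 84.6%), which gives 43.5% with the pooled z.

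**5. What 80% would take.**
- Patients at 2 years: (1.96 × √(2 × 0.89 × 0.11) + 0.842 × √(0.0564 + 0.1344))² / 0.10² = 153 per arm before dropout.
- Deaths: 4 × (1.96 + 0.842)² / (ln 2.82)² = 29.3, so 30 (Schoenfeld); 35 by Freedman.
- Detectable difference at 70 per arm: 94% vs 78% has 78.5% power and 94% vs 77% has 82.2%, so 16-17 points. At 63 per arm, 94% vs 77% has 78.0% and 94% vs 76% has 81.5%, so 17-18 points.

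**6. Longer follow-up, constant hazards.** Simulated log-rank power:
- Follow-up spread over 2-4 years, with 10% dropout: 60%
- Follow-up spread over 2-5 years, with 10% dropout: 66%
- 3 years for all: 63.7% at 70 per arm, 58.8% at 63
- 5 years for all: 83.6% at 70 per arm, 79.7% at 63

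**The case against.** The best defence is that the power sentence names no analysis time. It follows directly on a log-rank test, which uses all follow-up, and the Follow-up evaluation section runs to 5 years. If every patient completes 5 years at constant hazards, power is about 80%. By Schoenfeld's formula, 4 years for all 140 patients already gives 79% (28.8 deaths). That much is true, and the 45-50% figure is therefore conditional on analysis at 2 years.

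The defence does not save the statement. No later analysis time is given, and both the 94% and the endpoint are labelled 2-year. Schoenfeld is also optimistic at this hazard ratio: at 4 years Freedman gives 72%, and at 2 years Schoenfeld exceeds the simulation by about 5 points.

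Two further points stand in part. The comparison is secondary and the primary sample size is untouched, which limits the consequence. The protocol also plans no equivalence or non-inferiority conclusion between arms, so misreading a null result is a risk rather than a stated intention. Finally, it can be argued that correcting the number would be enough and that estimation wording goes further than the error requires. That wording is nonetheless cheap, and it guards against the misreading.

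**Conclusion.** The statement is wrong as written. At the protocol's own 2-year time point, 140 patients give about 45-50% power for 94% vs 84% at two-sided 0.05. Across the z, chi-square and log-rank methods the range is 46-53% at 70 per arm and 43-49% at 63; Fisher's test is lower. A true 10-point OS deficit would be missed about half the time.

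The two-proportion figures need no assumption beyond the stated rates. The log-rank figures assume proportional, constant hazards and ignore stratification. Power near 80% requires roughly 30-35 deaths, which at constant hazards means follow-up of about 5 years for essentially every patient. The error affects a secondary comparison; the one-sample design behind the 140 patients is sound on this point.

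**What to change.** In the Analysis plan, remove the 80% claim. State instead that 140 patients give about 45-50% power for 94% vs 84% at 2 years (two-sided 0.05), and about 80% only for a gap of roughly 16-18 points or once about 30 deaths have occurred (35 by the more conservative formula). If a later analysis was intended, give its timing or the number of deaths and reconcile it with the 2-year label under Secondary endpoints.

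Keep the stratified log-rank test, but present the between-arm OS result as estimation: hazard ratio and 2-year difference, each with a 95% confidence interval, with a sentence saying that a non-significant result is not evidence of similar survival. The precision is worth stating too: at 94% vs 84% with 70 per arm, the half-width for the 2-year difference is about 1.96 × 0.0522 = 10 points.

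The cost is protocol and SAP wording only. No extra patients are needed; the published power figure becomes less favourable.

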### Data safety monitoring committee

The data safety monitoring committee (DSMC), consisting of at least one surgical oncologist, one radiation oncologist, and one medical oncologist not involved in the study and without competing interests, will meet bi-annually after study initiation to review toxicity outcomes. The DSMC can recommend modification of the trial based on toxicity outcomes.

After half of the patients are enrolled and followed for 6 months, one interim analysis will take place. For this interim analysis, OS at 2-years will be calculated for each arm. The DSMC may recommend cessation or modification of the trial if any of these two criteria are met:
The rate of grade 5 toxicity definitely related to treatment is > 5% in either armThe upper bound of the 95% confidence interval of OS at 2 years does not include 94%.

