Since the ORATOR trial opened in 2012, the landscape has further shifted to recognize the clinical importance of HPV status. The impact of HPV on outcomes has been so substantial that a separate staging system has been created to better represent the prognosis of these patients [3, 14]. Although not yet part of routine clinical care, research is now focused on de-intensification of treatment in HPV+ OPC, in an attempt to reduce adverse events while maintaining excellent oncologic outcomes. Patients with HPV-related OPC have an excellent chance of survival, and therefore may have to deal with the sequelae of therapy for many decades [3]. With excellent rates of cure, post-treatment QOL becomes of paramount importance. Trials focusing on both primary RT and primary surgical approaches have de-escalated radiotherapy doses; two key trials that are currently underway include NRG-HN-002 and ECOG-3311 [15, 16].

NRG-HN-002 [15] included 308 patients in a phase II parallel-arm design investigating de-intensification in a low-risk p16+ population (T1–2 N1-N2b or T3 N0-N2b as per AJCC 7th edition, and ≤ 10 pack-year smoking history). Arm 1 was conventionally fractionated CRT with 60 Gy (2 Gy/fraction) given in 6 weeks with weekly cisplatin 40 mg/m^2^ and Arm 2 was accelerated RT alone with 60 Gy (2 Gy/fraction) given in 5 weeks with 6 fractions per week. The trial had co-primary endpoints with progression-free survival (PFS) and QOL at 2 years with acceptability criterion of PFS of ≥85% and an MDADI score ≥ 60. Early results presented in abstract format showed the CRT arm met the acceptability criteria for both PFS and MDADI, while the accelerated radiotherapy arm did not meet the PFS acceptability criterion [15].

ECOG-3311 focuses on a primary surgical approach for cT1–2 N1–2b (as per AJCC 7th edition) HPV+ OPC patients, de-escalating the adjuvant RT dose for intermediate risk patients based on surgical pathology. After resection, if a patient has any of: close margins, < 1 mm of extranodal extension (ENE), 2–4 lymph nodes (LN) involved, perineural invasion (PNI) or lymphovascular invasion (LVI) they are randomized in a 1:1 ratio to standard dose adjuvant RT (60 Gy) or de-escalated adjuvant RT (50 Gy). The primary endpoint for this trial is PFS. This trial has completed accrual, but results are not yet reported [16].

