Given the dramatic rise in the incidence of HPV disease and the paucity of high-quality data comparing treatment options, the management of HPV+ OPC is arguably the most contentious issue in head and neck oncology [17, 18]. The purpose of this randomized trial is to assess the safety of two de-escalation approaches (primary RT and primary surgery) in early T stage HPV+ OPC by comparing to historical control, and to compare survival, toxicity and QOL profiles between the two approaches. The primary radiotherapy approach is based on the chemoradiation arm of HN002, and the primary surgery approach is based on the treatment paradigm of ECOG-3311 [15, 16].

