#### Primary radiotherapy (Arm 1)

Treatment in this arm is generally based on Arm 1 of NRG-HN002 [15], and may consist of either radiotherapy alone or concurrent chemoradiation depending on the patient’s clinical nodal status (see Table 1).

**Table 1 Tab1:** Delivery of radiation ± chemotherapy depending on clinical nodal status in Arm 1 (Primary RT)

	Radiation Alone: Accelerated radiation	Concurrent chemotherapy: Weekly cisplatin 40 mg/m^2^ for 6 cycles
Nodal status	Node negative (N0) OR Single node less than 3 cm in maximal diameter	Multiple lymph nodes OR Single lymph node more than 3 cm in maximal diameter
Fractionation	Radiation over 5 weeks, with 6 fractions a week 6th weekly fraction given on a weekday with a minimum 6 h intrafraction interval, or on a Saturday	Daily radiation, Monday-Friday over 6 weeks
Special conditions	In patients > 70 years of age, standard fractionation (daily, Monday-Friday over 6 weeks) can be used at the discretion of the radiation oncologist	In patients who are deemed unfit for weekly cisplatin, the dose and/or schedule can be modified, or cetuximab or weekly carboplatin AUC 1.5 can be used, at the discretion of the medical oncologist.

Dose levels are as follows:
60 Gy in 30 fractions: Gross Tumor and Involved Nodes54 Gy in 30 fractions: High risk subclinical areas.48 Gy in 30 fractions: Low-risk nodal areas

Specific radiotherapy volume definitions for Arm 1 are described in Table 2. In all cases a 5 mm CTV to PTV expansion is to be used.

**Table 2 Tab2:** Specific RT volume definition volumes for Arm 1 (Primary RT)

Radiotherapy Volume	Definition
GTV_P	Gross tumour volume
GTV_N	Gross nodes: – > 1.5 cm long axis – > 1 cm short axis – Necrotic – PET positive
CTV60	Combination of GTV_P and GTV_N with a 5 mm expansion, excluding natural boundaries of spread
CTV54	– A 1 cm expansion on the GTV_P – Any nodal level that contains a positive node. – Any node < 1 cm in short axis the radiation oncologist deems suspicious for harbouring disease. This node plus an additional 5 mm margin will be included in the CTV54. – The first echelon draining nodal levels. This is nearly always level 2, but should include the lateral retropharyngeal nodes (RP) for soft palate and posterior pharyngeal wall extension.

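### DSMC monitoring includes nothing on progression, although the protocol calls 2-year PFS below 75% unacceptable; a progression table and a non-binding PFS trigger would be a cheap improvement

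*Protocol article*

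**What the plan says.** All references are to the protocol article.

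- **Data safety monitoring committee, regular meetings.** The committee meets twice a year to look at toxicity. "The DSMC can recommend modification of the trial based on toxicity outcomes".
- **Same section, interim.** The timing is fixed by enrolment and minimum follow-up: "After half of the patients are enrolled and followed for 6 months, one interim analysis will take place". The only efficacy measure named for that look is survival: "For this interim analysis, OS at 2-years will be calculated for each arm". The list of grounds is closed: "The DSMC may recommend cessation or modification of the trial if any of these two criteria are met". The two grounds are a rate of grade 5 toxicity (definitely treatment-related) above 5% in either arm, and a 95% confidence interval for 2-year OS whose upper bound falls short of 94%.
- **Analysis plan.** Expected 2-year PFS is about 85%. "If the 2-year PFS is < 75%, it will be considered unacceptable". Each arm is tested against 74% at the end of the trial. No interim use of this limit is described.
- **Primary endpoint.** OS replaced PFS as primary because, in the preceding trial, progression could often be salvaged.
- **Background and Table 1.** In the cited NRG trial, the chemoradiation arm met its criteria, "while the accelerated radiotherapy arm did not meet the PFS acceptability criterion". Table 1 gives node-negative and single-small-node patients in Arm 1 a radiotherapy-alone schedule of the same form: "Radiation over 5 weeks, with 6 fractions a week".
- **Salvage surgery.** Salvage within 5 months of treatment is scored as persistent disease and not as recurrence.

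**The concern.** When treatment is reduced, the main added risk is loss of disease control. The protocol sets a PFS level that it regards as unacceptable, but nothing connects that level to monitoring during the trial. The interim criterion that could pick up a failing arm is OS. By the protocol's own account progression is often salvaged, so deaths will come later than recurrences and there will be fewer of them. Followed as written, an arm with excess recurrence but few early deaths meets neither criterion, and the regular meetings are not described as seeing progression data at all. At stake is whether the DSMC could notice gross loss of disease control while patients are still being enrolled.

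**Working it through.** **1. Inputs from the protocol.** 140 patients, 1:1, 70 per arm. That figure reproduces: an exact one-sided binomial test of 94% against 84% needs 63 evaluable patients (at least 58 alive; alpha 0.049, power 0.824), and 63/0.90 = 70. The interim takes place at half the enrolment: 140/2 = 70 patients, about 35 per arm, each followed for at least 6 months. PFS limit 75%, expected PFS 85%, expected OS 94%.

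**2. Assumptions, not in the protocol.** Constant hazards; the first 70 patients enter uniformly over A = 12, 18 or 24 months; no loss to follow-up. Follow-up at the interim then runs uniformly from 6 to 6 + A months.

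**3. Expected events.** With 2-year survival S, the hazard is λ = −ln(S)/2 per year. With A in years, the average probability of an event by the interim is

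q = 1 − [exp(−0.5λ) − exp(−(0.5 + A)λ)] / (λA).

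Example, S = 0.75 and A = 1: λ = 0.1438; q = 1 − (0.9306 − 0.8059)/0.1438 = 0.133; 35 × 0.133 = 4.7 events.

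| Expected events among 35 | A = 12 | A = 18 | A = 24 |
|---|---|---|---|
| PFS events, true PFS 85% | 2.7 | 3.4 | 4.0 |
| PFS events, true PFS 75% | 4.7 | 5.7 | 6.7 |
| PFS events, true PFS 60% | 7.8 | 9.4 | 10.9 |
| Deaths, true OS 94% | 1.1 | 1.3 | 1.6 |

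An arm at 60% PFS whose recurrences are salvaged would thus show about 8 to 11 PFS events beside 1 or 2 deaths.

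**4. The existing OS criterion.** As an illustration that favours the rule, suppose all 35 patients have known 2-year status. With an exact 95% interval, the upper bound first drops below 94% at 6 deaths (29/35 alive = 82.9%, upper bound 93.4%). If true OS is 94%, this happens with probability 0.017. It depends on deaths alone, so it stays 0.017 at any recurrence rate that leaves OS at 94%.

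**5. A trigger on PFS.** Flag an arm when its event count reaches the smallest k with P(X ≥ k) ≤ 0.10, where X is binomial(35, q) and q is taken at 75% PFS. This gives k = 8, 10 and 11 for A = 12, 18 and 24.

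| True 2-year PFS | A = 12 | A = 18 | A = 24 |
|---|---|---|---|
| 85% | 0.005 | 0.001 | 0.001 |
| 75% | 0.085 | 0.048 | 0.057 |
| 74% | 0.10 | 0.06 | 0.07 |
| 70% | 0.20 | 0.14 | 0.16 |
| 65% | 0.36 | 0.29 | 0.34 |
| 60% | 0.54 | 0.47 | 0.55 |
| 50% | 0.84 | 0.82 | 0.87 |

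These are probabilities per arm. At 85% in both arms, the largest per-trial false-flag rate is 1 − (1 − 0.0047)² = 0.009.

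**6. The 5-month scoring rule.** In Arm 1, radiotherapy lasts 5 to 6 weeks and starts within 4 weeks of randomization. If the 5 months run from the end of radiotherapy, the window closes at the earliest after 5 weeks + 5 months, about 6.2 months from randomization, and at the latest after 10 weeks + 5 months, about 7.3 months. A patient with only 6 months of follow-up is still inside it, so salvaged local or nodal disease would not yet count. A constant hazard from randomization therefore probably overstates early countable events in Arm 1. The documents do not allow the size of this to be calculated.

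**The case against.** The strongest reply is that the omission follows from a stated choice. PFS was deliberately demoted because progression can be salvaged, an OS-based interim is consistent with that, and the 75% figure belongs to a secondary test at the end of the trial. This stands as a defence of OS as the primary endpoint. It does not explain why the DSMC should be shown no progression data, and the same salvage argument is the reason early OS is a weak signal of recurrence.

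A second reply is that the proposed trigger is weak near 75%. That is true: an arm at 70% would be flagged in only 14–20% of cases. It can detect gross failure and nothing finer.

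Third, both existing criteria are advisory, deaths from recurrence do count towards OS, and a DSMC charter might add tables. So it cannot be said that an unacceptable arm would necessarily enrol to completion. The article does, however, word its interim criteria as a list of two.

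Two stronger readings are tempting, and the documents support neither:

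- A reader might take the cited accelerated-radiotherapy result as evidence that part of Arm 1 will fall below 75% PFS. The criterion missed there was 85% or more, in a different stage mix (T1–2 N1–N2b or T3 N0–N2b under AJCC 7th edition, at most 10 pack-years). Table 1 uses the schedule for T1–2 patients with no node or one small node. The result is a reason to display the subset separately and shows nothing about the 75% limit.
- A reader might see a contradiction between "The primary radiotherapy approach is based on the chemoradiation arm of HN002" and Table 1. No section says that Arm 1 rests solely on the chemoradiation arm. Study design, Primary radiotherapy (Arm 1) and Discussion all disclose that chemotherapy is conditional, so no correction is needed there.

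**Conclusion.** The point holds as a cheap improvement to monitoring; it is not an error in the endpoint or the sample size. The DSMC section contains no progression measure, the Analysis plan contains a PFS level called unacceptable, and the OS criterion can stay silent while recurrences accumulate (0.017 chance of firing at 94% OS, under full 2-year follow-up). A PFS trigger at the interim would flag 47–55% of arms at 60% PFS and 82–87% at 50%, but only 29–36% at 65%, 14–20% at 70% and 6–10% at 74%. All of this assumes 35 patients per arm, constant hazards and 12 to 24 months' accrual plus 6 months, and is less certain for Arm 1 because of the 5-month scoring rule. The size of the radiotherapy-alone subset is not given, so its counts can only be descriptive. Nothing here bears on which radiotherapy schedule is right.

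**What to change.** In the Data safety monitoring committee section:

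1. Give the DSMC progression and PFS event counts per arm at every twice-yearly meeting and at the interim, descriptively, with Arm 1 split into radiotherapy alone and chemoradiation.
2. Add a non-binding trigger for DSMC discussion at the interim: an arm is referred when its PFS events exceed the number expected over the follow-up actually accrued at the protocol's 75% 2-year limit, at a one-sided 10% level. Recompute the threshold from the real follow-up times; 8, 10 and 11 of 35 are illustrations.
3. Count events as the two salvage surgery sections define them, so that salvage within 5 months is not scored as recurrence, and state that this can delay counting in Arm 1.
4. State the trigger's limits: it detects gross failure only, and an arm that is not flagged has not been shown to be above 75%.

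OS stays primary, and the sample size, treatment and existing two criteria are unchanged. Progression is already recorded on the case report form (Disease progression and new primary), so the cost is one extra DSMC table and a few lines of text. The statistical price is a false flag in up to about 0.5% of arms, or about 0.9% of trials, when true PFS is 85%; for an arm exactly at 75% it is about 5–9%. A flag leads to a discussion and stops nothing by itself.
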